# Evaluation of telemental health services for people with intellectual and developmental disabilities: protocol for a randomized non-inferiority trial

**DOI:** 10.1186/s12913-023-09663-6

**Published:** 2023-07-25

**Keywords:** Disability, Crisis, Mental health, Telehealth, Autism, Virtual

## Abstract

**Background:**

Roughly 40% of those with intellectual/developmental disabilities (IDD) have mental health needs, twice the national average. Unfortunately, outpatient mental health services are often inaccessible, increasing reliance on hospital-based services. While telemental health services hold potential to address this gap, little is known about the effectiveness of telemental health for the diversity of persons with IDD, especially as it relates to crisis prevention and intervention services. Accordingly, the aims of this study are to: (1) compare telemental health versus in-person crisis prevention and intervention services among people with IDD; and (2) understand if outcomes vary across subpopulations, in order to identify potential disparities.

**Methods:**

This study will take place within START (Systemic, Therapeutic, Assessment, Resources, and Treatment), a national evidence-based model of mental health crisis prevention and intervention for people with IDD. A total of 500 youth and adults, located across nine states, will be randomized 1:1 to telemental health vs. in-person. Participant inclusion criteria are ages 12–45 years, living in a family setting, and newly enrolled (within 90 days) to START. Outcomes will be assessed, using a non-inferiority design, for up to 1 year or until discharge. The intervention is comprised of four components: (1) outreach; (2) consultation/coping skills; (3) intake/assessment; and, (4) 24-hour crisis response. The in-person condition will deliver all components in-person. The telemental health condition will deliver components 1 & 2, via telephonic or other communication technology, and components 3 & 4 in-person. Outcomes include mental health crisis contacts, mental health symptoms, emergency psychiatric service use, perceived quality of mental healthcare, and time to discharge.

**Discussion:**

To our knowledge, this will be the first trial of a telemental health crisis program for the IDD population. The study will be executed by an interdisciplinary team of experts that includes persons with lived experience of disability. Understanding the benefits of specific telemental health methods has important implications to the design of interventions. This telemental health study offers promise to address disparities in access to mental health care for people with IDD across diverse racial, ethnic, linguistic, and cultural groups.

**Trial Registration:**

Clinicaltrials.gov (#NCT05336955; Registration Date: 4/20/2022).

## Background

Roughly 40% of those with Intellectual/ Developmental Disabilities (IDD) have mental health needs, which is twice the national average [1, 2]. Unfortunately, equitable access to mental health care for this population does not meet the demand [3]. Untreated mental health symptoms among those with IDD is associated with emergency psychiatric service use and police involvement [4, 5]. For instance, numerous studies have found psychiatric hospitalizations and emergency department admissions are more common for those with IDD when compared to people without IDD [4, 6]. This can result in “boarding,” a situation where the individual spends an extraordinary amount of time (often weeks to months) awaiting an inpatient bed while remaining in the emergency department [7]. Use of emergency room services is not only costly and ineffective, but it is traumatizing to all involved.

The Developmental Disabilities Assistance and Bill of Rights Act of 2000 defines a developmental disability as a condition that is attributable to a mental and/or physical impairment, manifested before the age 22, long-term, results in significant limitations in multiple areas of functioning, and requires specialized supports [8]. Developmental Disabilities reflects a broad range of conditions, such as Autism Spectrum Disorder, Attention Deficit-Hyperactivity Disorder, and Cerebral Palsy [9]. The term developmental disability is often used interchangeably with other labels like neurodevelopmental conditions. However, Intellectual Developmental Disorder is a more specific condition that falls under the umbrella of developmental disabilities. Defined by the 5th edition of the American Psychiatric Association’s Diagnostic and Statistical Manual, Intellectual Developmental Disorder involves impairments in general mental ability that impacts adaptive functioning in social, academic, and self-management skills [10]. This term, created by the American Psychiatric Association, was created to replace the label Intellectual Disability. Given the population described above includes is a highly heterogeneous group, we use the term intellectual/developmental disabilities (IDD) hereafter to reflect all of these persons.

Use of telehealth services has gained prominence as an opportunity to address gaps in mental health services, especially since the COVID-19 pandemic. There is a growing body of research pointing to the effectiveness of telemental health to treat diverse populations for a range of conditions such as depression, anxiety, and eating disorders [11]. However, evidence for the effectiveness of telemental health among persons with IDD is sparse. Telemental health research conducted among this group has predominately focused on the delivery of ABA-based services [12–14], although none of those designs were experimental. A recent virtual mindfulness training program for people with IDD demonstrated positive outcomes, but once again this study was observational [15]. Studies that have deployed randomized designs among persons with IDD have examined cognitive behavioral therapy [16], functional communication [17], and mindset-based interventions [18]. While all these studies demonstrated clinical improvements, their samples were quite small and limited in terms of racial, ethnic, and/or cultural diversity. As a result, a recent systematic review concluded that the current body of research was not sufficient to demonstrate “effectiveness of telehealth-based digital intervention in improving the situation among people with disabilities” [19]. The present study will help fill this gap by evaluating a large scale, systems-based telemental health intervention for a diverse population of people with IDD using a randomized design.

The study will take place in the START (Systemic, Therapeutic, Assessment, Resources, and Treatment) network. START is an evidence-based, cross-systems crisis prevention and intervention model for people with IDD who have mental health needs. First developed in 1988, START has been cited by the National Academy of Sciences and Engineering as a promising model to help overcome disparities in access to mental health care for persons with IDD [20]. In 2008, the Center for START Services was established at the University of New Hampshire Institute on Disability/University Center for Excellence on Disability, College of Health and Human Services.

Several studies have demonstrated positive outcomes associated with the START program. Two studies have shown 1-year pre-post improvements in: (a) service recipient mental health symptoms, as measured by the Aberrant Behavior Checklist; (b) family caregiver perceived quality of care; and (c) decreases in emergency room visits and psychiatric hospitalizations [21, 22]. Notably, these findings were consistent across regions (e.g., Northeast, South, Midwest), populations (e.g., Hispanic and Non-Hispanic), and geographic locale (urban, suburban, rural). A third, much larger study (N = 1,188) examined the timing and outcomes of mental health crises across the national START model [5]. While an increase in contacts was observed in the initial three months of enrollment, which is not surprising given service users and families are enrolled in times of need, there was a steep drop off thereafter with few crises occurring after one year. Importantly, about three out of four crises resulted in maintaining the person in their home.

Like most healthcare services, START had to rapidly transition to telehealth service delivery in response to the COVID-19 pandemic. Preliminary internal data from START indicated that telehealth was an effective method of START service delivery during that time (e.g., 85% of START service users who experienced a crisis maintained their setting). However, the lockdown and other unique societal conditions during pandemic undermine the ability to render these findings generalizable. This study aims to examine the benefits of telehealth as an effective option of service delivery for people enrolled in START and what, if any, methods or conditions contribute to outcomes.

## Methods

### Study aims

The primary aim of this study is to compare the effectiveness of in-person START practices versus START telemental health using a randomized control, non-inferiority design. It is hypothesized that telemental health START will not be inferior to in-person START in the reduction of emergency psychiatric service use, time-to-discharge, improvement in mental health stability and perceived quality of care. This finding will support the use of telemental health practices as a valuable alternative to in-person care.

A secondary aim of this study is to evaluate heterogeneity of treatment response by assessing differences in outcomes across diverse groups, including race, ethnicity, language spoken, rural settings, and level of intellectual disability. It is hypothesized that telemental health will not be inferior to the in-person condition across diverse groups, except for those living in rural settings. We hypothesize improved perceived quality of care will be found among those in the telemental health condition who live in a rural setting, compared to those living in a rural setting who are in the in-person condition, given the known difficulty in accessing in-person services for those living far from care. This finding will support equitable effects of telemental health START practices among diverse racial/ethnic and developmental groups, with potential added value for those living in rural settings.

### Stakeholder engagement

This project brings together stakeholders with a shared commitment to improve telemental health services for individuals with intellectual and developmental disabilities and mental health needs (IDD-MH) from diverse backgrounds and perspectives. We define engagement as the process of working collaboratively with a group of people with diverse characteristics who are linked by social ties, share common perspectives, and engage in joint action toward a particular cause [23]. From design to dissemination of outcomes, our project is grounded in multi-level engagement of a variety of stakeholders in three different ways [23]. First, our Leadership Team includes an individual with IDD-MH, as well as researchers who are family members of people with disabilities. Second, Engagement Teams partnered in the design of research processes and materials to ensure the approach is inclusive of diverse individuals with a range of disabilities, educational, and literacy levels. The Engagement Team meets every other week, and includes people with IDD-MH, family members, START clinicians, and members of our research team. Third, an Advisory Council meets quarterly to provide expert feedback to optimize the importance, feasibility, and accessibility of research processes and outcomes for diverse stakeholders. The Advisory Council includes people with IDD-MH, family members, mental health professionals, researchers with expertise in the mental health and wellbeing of people with IDD, and healthcare policy makers. Finally, throughout the project, we connect with people and families served by START and START providers to build their capacity to engage in research, enhance feasibility, and share what we learn.

### Setting and inclusion criteria

The study will take place in nine states across the US. Within each state, the number of START programs range from 1 to 8 (see Table 1 for details). A total of 500 youth and young adults receiving START services will be enrolled for up to one year or until discharge. Participant inclusion criteria are ages 12–45 years, living in a family setting, and newly enrolled (within 90 days) START service user. The first participant will be enrolled in Spring 2023. The current status of this trial is pending. The study is expected to be completed by 2026.

**Table 1 Tab1:** Recruitment States and Sites

State	Number of Sites
California	8
Colorado	1
New Mexico	1
New Hampshire	3
New York	5
North Carolina	3
Pennsylvania	1
Tennessee	5
Texas	1

### Intervention

START is a complex, multi-component intervention that includes four core elements: (1) outreach, service linkages, referrals, and training; (2) consultation and coping skill coaching; (3) intake and quarterly assessment; and, (4) 24-hour crisis response and intervention [21, 22]. As seen in Fig. 1, these components are based on START’s conceptual model, which is theory-driven and evidence-based. START teams consist of START Coordinators (master’s in social work or counseling) with caseloads of 20–30 people. The team also has a Clinical Director (PhD Clinical Psychologist), a Medical Director (Psychiatrist and/or Child Psychiatrist), and therapeutic coaches (BS/BA).

**Fig. 1 Fig1:**
[figure not shown]
Conceptual Model: START In-person and Telemental Health

#### Component 1: Outreach, service linkages, referrals, & training

START teams work with stakeholders to develop and maintain linkage agreements [21, 22]. The purpose of these agreements is to enhance the capacity of the system as a whole and develop partnerships to reduce disparities and gaps in the service array [21, 22]. START coordinators conduct crisis prevention-focused outreach visits with the person and/or their system of care. Examples include training during home- and school-based visits, family caregiver coaching to implement new plans or strategies, and checking in with the person to monitor their level of stability.

#### Component 2: Consultation & coping skills coaching

Mental health service consultation is provided by START clinical and medical directors to prevent and de-escalate crises [21, 22]. Coping skills coaching helps to determine with the person, their family, and the system of care, how to promote well-being and stability. Successful coping and de-escalation practices for the person are incorporated into the Cross-Systems Crisis Prevention and Intervention Plan. All methods have shown value when provided in person. During COVID 19, these services were provided via telehealth with promising outcomes. As part of the current study, separate focus groups with family members, START staff, and START service users were held to better define how to apply these practices via telehealth, and START teams will be trained in order to maximize telehealth effectiveness prior to the randomized control trial.

#### Component 3: intake and quarterly assessment

The START Plan is a custom assessment designed to evaluate the mental health needs of persons with IDD and measure the capacity of the formal and natural support systems [21, 22]. Family caregivers, or the person primarily responsible for day-to-day care of the person, participate in a standardized, 30-60-minute interview conducted by START coordinators. The START coordinator completes the initial START Plan during intake and quarterly thereafter. Quarterly assessment is conducted to inform development or modification of the Cross-Systems Crisis Prevention and Intervention Plan.

#### Component 4: 24-hour urgent crisis response and intervention

START teams have 24-hour, in-person mobile crisis intervention services [21, 22]. Emergency calls come from a variety of sources, including START service users, emergency rooms, service providers, families, and law enforcement. START provides immediate telephonic response and in-person evaluation within two hours of the initial contact.

### Cross-systems crisis prevention and intervention plan

As seen in Fig. 1, the Cross-Systems Crisis Prevention and Intervention Plan provides a comprehensive, person centered, culturally and linguistically accessible roadmap to both prevent crises and intervene in times of acuity. Based on a tertiary care approach to treatment, the plan is designed to deliver a strategy to build capacity to encourage coping skills and address challenges, attain assistance from outside the home/school setting, and respond in times of more urgent need. The plan is developed based on assessments, coaching, outreach, and training provided by the START team in close collaboration with the START service user and the system of support. A member of the START team facilitates the development, review, and revision of the Cross Systems Crisis Prevention and Intervention Plan, with stakeholders engaged throughout the process.

### Comparators

This study compares in-person vs. telemental health START services. For in-person, this comparator will deliver all services and supports to persons with IDD and their families in-person, often in their homes. This is standard START practice. Due to the increased use of telecommunications in the field of healthcare, particularly since the COVID-19 pandemic, individuals in the in-person condition may have large healthcare planning meetings using telecommunication platforms such as Zoom^(TM)^. Use of telecommunications for healthcare planning, such as coordinating care and creating service linkages, will be tracked and assessed throughout the study. The telemental health condition will deliver components 1 & 2 via telephonic or other communication technology and components 3 & 4 in-person. Intake and quarterly assessment (component 3) and 24-hour urgent crisis response and intervention (component 4) will be provided in-person because this is needed to establish therapeutic rapport and ensure the safety of people with IDD and their families.

### Fidelity

All START teams are trained and certified by the Center for START Services for model fidelity. Fidelity to the model is assessed in three primary ways. The first is through extensive training, education, and dialogue. Given the lack of graduate education that addresses the mental health aspects of IDD, ongoing professional development, training, and quality review are needed to ensure competency across START teams. The Center for START Services also provides clinical apprenticeship opportunities, practice improvement groups, community training, and cross-systems engagement. The second approach is to monitor fidelity to START practices through the Center for START Service’s database. Third, is ongoing research and evaluation to continuously assess and improve START methods via analysis of outcomes as reported in the START database, also termed SIRS (see below).

#### Data capture and entry

START employs total quality improvement approaches including the START Information Reporting System (SIRS), a robust and secure data collection, reporting, and evaluation infrastructure. START teams are trained to accurately enter data into SIRS using a comprehensive data dictionary. The quality and frequency of data entry is closely monitored by the Center for START Services, where data are housed. Data from SIRS will be used for this analysis.

### Assessments

Emergency service use and time-to-discharge will be assessed continuously throughout the 1-year study time line. All other assessments will be done at baseline, 6 (midpoint) and/or 12 (outcome) months, except for the START plan (which is conducted quarterly), the Family Experiences Interview, and the Person Experiences Interview (conducted at pre-post).

#### Mental health crises and emergency service use

The primary outcome for this study is use of and diversion from emergency mental health services. This includes emergency department visits and in-patient hospitalizations, including length of stay and police/jail involvement, and number of 24-hour START in-person crisis contacts. All of these data are gathered by the START Coordinators in the SIRS database.

### Perceived quality of mental healthcare

#### The family experiences interview schedule

The second outcome is family caregiver evaluation of their experiences with the mental healthcare system. This is assessed via the Family Experiences Interview Schedule (FEIS), a widely used semi-structured interview [24]. Baseline FEIS interviews are conducted by the START coordinator in the ordinary START intake process. Follow-up interviews will be conducted by an individual who was not involved with the person’s care. Interviews take approximately 20 min to complete. Three FEIS subscales will be used. The first (9 items) assesses family members’ appraisal of their own involvement as partners in treatment, the second Sect. (7 items) assesses perceived quality of services provided to the recipient, and the final Sect. (4 items) elicits feedback about how well the mental health system responds to the needs of family caregivers. Previous research across multiple samples has shown the FEIS and these subscales to be reliable (Cronbach’s α = 0.92) and internally valid [21].

### The person experiences interview schedule

To ensure our study includes outcomes reported from the perspectives of people with IDD, we are designing a novel patient-reported outcome measure called the Person Experienced Interview Schedule (PEIS). This measure is critical since the FEIS relies on family caregiver informants who may not share the same perspective as youth and young adults with IDD. The PEIS will be adapted from the FEIS. We have chosen to adapt the FEIS because: (1) it is brief; (2) it focuses on perceived quality of mental healthcare, a critical outcome of this study; (3) to our knowledge, no measures are available for this outcome that can be used for persons with IDD; and (4) it directly aligns with the goals of the START model. Our adaptation process is following best practice, patient-reported guidelines put forth by COSMIN. Details of this measure will be reported in forthcoming publications. Its design and ethical use has been approved by the governing Institutional Review Board.

#### Mental health symptoms

The Aberrant Behavior Checklist – Community Version will be used to measure problem behaviors associated with mental health symptoms [25, 26]. The ABC is a well-known and psychometrically robust measure that was designed specifically for persons with ID. The Irritability, Lethargy, and Hyperactivity subscales will be the focus of this study. Family caregivers serve as the informant.

Mental health stability, as measured in the START Plan, is comprised of (1) intensity of mental health symptoms and (2) risk to self or others. Symptoms encompass 16 items, such as verbal and physical aggression, suicidality, anxiety, depression, psychosis, and trauma-related symptoms, all of which are rated on four-point scale from “no concern” to “high concern.” Risk to self or others is determined with 7 items, which reflect behavioral acuity, as rated on a four-point scale of “rarely” to “often.” Raw scores are summed to create the composite score, associated with four categories of instability: stable, low, moderate, and high.

#### Time-to-discharge

The final outcome is time to discharge. Discharge occurs when the person no longer is at high risk for mental health emergency service use. Discharge is determined in collaboration with the person, their family caregiver, and their interdisciplinary team. It is an indicator of mental health stability. This indicator will be measured as the difference in days between START admission and discharge.

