### Masking, randomization, and data safety monitoring

Based on feedback from family and provider stakeholders gathered during the development of this proposal, participants will not be masked. Randomization will occur at the individual level using a random number generator in blocks of two to ensure that participants within the settings are allocated equally to conditions. Randomization will be conducted by an independent party and study coordinators will be unaware of the randomization allocation until participant enrollment. Allocation will be revealed via a blinded excel file after participant enrollment. This study adheres to the SPIRIT guidelines.

We have developed an ethically approved data safety and monitoring plan. This plan involves obtaining informed and written consent from the guardian(s) as well as assent from all participants, by the designated research coordinator, and safely storing data and restricting unauthorized access to identifiable participant information. Additionally, this plan outlines the protocol for responding to any adverse events/reactions to the randomly assigned treatment options. While this study is low-risk, there is a limited possibility that participants in this study will experience unknown effects. Therefore, the study team will closely monitor the acceptability of the procedures and seek to understand any concerns from participants and guardian(s) to ensure they are addressed in a timely matter. If a formal concern is voiced by a participant or by their guardian(s), which is possible at any time (via provided study contact information), it will be immediately addressed to the best of the study team’s ability and will also be reported to the ethics board. Discontinuation of the study protocol will be made at the participants’, ethics board, and/or monitoring boards’ request. No specific modifications are considered at the present time.

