### Statistical analyses

The efficacy analyses will be conducted as both intention-to- treat (ITT; “as allocated”) and per protocol (PP; “as-treated”) since ITT can bias towards the null, leading to false claims of non-inferiority, and PP can fail to preserve the balance inherent to randomization (30, 31). For the analysis, the first step will be to examine demographic and clinical characteristics across study conditions to assess that the randomization worked as expected. If significant sociodemographic differences emerge, these variables will be included in the multivariate analyses since baseline adjustment has been shown to increase precision in randomized control trials (32). All analyses, for the factorial design, will be examined using a series of multilevel (or “mixed” effects) general linear regression models that account for clustering (via a random intercept) across sites. For these models, the independent variable of interest will be telemental health versus in-person START. The dependent variables will be calculated as change scores/differences since baseline. Two-way (Intervention group x time) interaction terms will test the primary study aim. Three-way (Intervention group x demographic population x time) interaction terms will test the secondary study aim. Effect sizes will be calculated using Cohen’s *d*. To accommodate increased false discovery rate, the study will adjust the significance threshold using the Benjamini-Hochberg procedure. This procedure is conducted after all tests are concluded; α = .01 will be assumed for the power analysis.

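### Time-to-discharge is counted from START admission, although randomisation can follow up to 90 days later; the origin should be randomisation, and the start of the one-year window should be stated

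*Protocol article*

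**What the plan says.** All of this is in the protocol article.

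- **Origin of the outcome** (Time-to-discharge): "This indicator will be measured as the difference in days between START admission and discharge".
- **Entry** (Setting and inclusion criteria): a participant is a "newly enrolled (within 90 days) START service user".
- **Allocation** (Masking, randomization, and data safety monitoring): "Allocation will be revealed via a blinded excel file after participant enrollment".
- **Length of follow-up** (Setting and inclusion criteria): participants "will be enrolled for up to one year or until discharge". The Assessments section adds: "Emergency service use and time-to-discharge will be assessed continuously throughout the 1-year study time line". Neither statement says which date starts the year.
- **FEIS baseline** (The family experiences interview schedule): "Baseline FEIS interviews are conducted by the START coordinator in the ordinary START intake process". Outcomes are then analysed as changes (Statistical analyses): "The dependent variables will be calculated as change scores/differences since baseline".

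Nothing in the article mentions delayed entry, a baseline renewed at randomisation, or adjustment for the lag between START admission and randomisation.

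**The concern.** The admission origin is a stated definition, not a detail left to a later document. Someone randomised on day 85 brings 85 days into the outcome that belong to neither arm. The care in those days is presumably in-person for everyone, since the Comparators section calls in-person delivery standard START practice. Nobody can have been discharged in that time, because a discharged person would no longer be a START service user able to enrol.

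These days vary between participants for reasons unrelated to treatment, so they add noise. They could do more harm if they also use up part of the one-year window. Each late entrant would then have less randomised follow-up, and any true difference between arms would have less time to appear. Study aims includes time-to-discharge in the non-inferiority hypothesis, and attenuation towards no difference favours that conclusion.

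The lag also covers an unsettled period for crises. Of earlier START data, the Background says: "While an increase in contacts was observed in the initial three months of enrollment", followed by a steep fall. That observation concerns crisis contacts, so it says nothing direct about discharge or FEIS.

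**Working it through.** **No figure to reproduce.** The article gives no margin, sample size or power for time-to-discharge. The sizes below rest on assumptions, labelled as such.

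**1. Share of the interval.** With the largest permitted lag, 90/365 = 24.7% of a year counted from admission precedes randomisation. If lags are uniform on 0 to 90 days (assumption), the mean is 45 days, or 45/365 = 12.3%, and the lag adds an SD of 90/√12 = 26.0 days.

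**2. Year counted from admission.** Assume constant hazards, with 40% of one arm and 30% of the other discharged within 365 days of randomisation.

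- Hazards: h₁ = −ln(0.6)/365 = 0.0013995 and h₂ = −ln(0.7)/365 = 0.0009772 per day.
- Restricted mean time over t days: RMST(t) = (1 − e^(−ht))/h.
- Full year after randomisation (t = 365): 307.0 − 285.8 = 21.2 days.
- Day-90 entrant, left with t = 275: 241.1 − 228.3 = 12.9 days (from unrounded values), which is 1 − 12.9/21.2 = 39% smaller.
- Averaged over t = 365 − u with u uniform on 0 to 90: 16.9 days, which is 1 − 16.9/21.2 = 20% smaller.

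All of this shrinkage comes from the lost follow-up after randomisation. Adding the same distribution of lag to both arms does not itself change a difference in means.

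**3. Separating the origin from the window.** A simulation with 400,000 participants assumed exponential discharge, a hazard ratio of 0.70, a uniform lag of 0 to 90 days and 60% of the in-person arm discharged by one year.

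| Measurement | Difference (days) | Ratio of means | Cohen's d | HR |
|---|---|---|---|---|
| From randomisation, 365 days | 30.6 | 1.128 | 0.241 | 0.701 |
| From admission, 365 days after randomisation | 30.5 | 1.107 | 0.235 | 0.702 |
| From admission, year also from admission | 25.0 | 1.094 | 0.227 | 0.700 |

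If every lag is 90 days, the last row's difference is 19.4 days, against 30.3 from randomisation. The hazard ratio is nearly constant throughout. The difference in days falls materially only in the third row. Moving the origin alone (second row) pulls the ratio of means towards 1 and lowers d slightly.

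**4. FEIS.** If follow-up is a fixed time after randomisation, improvement under shared care before randomisation is balanced between arms and drops out of the expected difference in change. If the follow-up FEIS is instead timed 12 months from intake, and an arm difference builds up linearly (assumption), a true deficit of 7 points at 365 days appears as 7 × (365 − lag)/365:

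- 45-day lag: 7 × 320/365 = 6.14 points.
- 90-day lag: 7 × 275/365 = 5.27 points.

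The Non-inferiority design section equates 7 points with 0.5 SD, which implies SD = 14. Ignoring clustering, SE = 14√(2/n), which is 1.75 at 128 per group and 1.25 at 250. The chance that the lower 99% limit clears −7 is Φ((7 − observed deficit)/SE − 2.576):

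| Lag | n = 128 per group | n = 250 per group |
|---|---|---|
| 0 days | 0.005 | 0.005 |
| 45 days | 0.019 | 0.030 |
| 90 days | 0.056 | 0.116 |

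These rates apply only if follow-up is timed from intake, which the article does not state.

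**The case against.** The strongest reply is that the damaging case needs a premise the article does not contain. Being enrolled for up to a year, and a one-year study timeline, read more naturally as a year from study entry. On that reading the admission origin moves the difference from 30.6 to 30.5 days and the hazard ratio from 0.701 to 0.702. That stands, and it is why the dilution is stated here as conditional.

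A reader might also infer any of the following, and the document does not support them:

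- **Immortal-time bias favouring one arm.** The event-free period before randomisation has the same expected distribution in both arms, so it favours neither.
- **Noise that makes a false non-inferiority claim easier.** Against a fixed margin, extra variance widens the interval and makes non-inferiority harder to show. Only attenuation of the difference works the other way.
- **A biased FEIS comparison.** Shared care before randomisation cancels in expectation. An older baseline costs precision and does no more unless follow-up is timed from intake.
- **The same fault in every outcome.** Nothing places emergency service use, the ABC or the PEIS at START admission, and the Assessments section already puts emergency use within the study timeline.

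It is also fair to say that time-to-discharge is the last-listed outcome, without a margin or power calculation, and that 90 days is a ceiling. The typical lag is not given. These points limit the severity. They do not make admission the right origin for a randomised comparison.

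**Conclusion.** The point holds in a limited form. The stated definition puts up to 90 days of event-free time before randomisation into the outcome, and the article does not reconcile it with the one-year window. With a full year of follow-up after randomisation, the cost is a small loss of precision: d falls from 0.241 to 0.235 in the simulated scenario, with the day difference and hazard ratio essentially unchanged. If the year also starts at admission, the difference in days is diluted by about 20% on average and 39% for a day-90 entrant, in the direction that favours non-inferiority. Those percentages assume constant hazards, 40% versus 30% discharged in a year and, for the average, a uniform lag. For FEIS the issue is lost precision, and becomes dilution only if follow-up is timed from intake. The severity is should-fix and minor: an avoidable ambiguity, not a demonstrated bias.

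**What to change.** - Define time-to-discharge as days from randomisation to discharge.
- State that the one-year follow-up window, and the 12-month follow-up FEIS, are timed from randomisation.
- Include days from START admission to randomisation as a covariate in the time-to-discharge and FEIS change models. It is fixed before allocation, so adjusting for it is safe.
- Report days from admission descriptively, to keep a link with earlier START work.

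The change is to wording and uses dates that the trial will already hold. The cost is slightly less comparability with START reports that count from admission.
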